### 2.8. Data management

All pseudonymized research data, including demographics, laboratory data, questionnaire responses, and AE records, will be recorded in the case report form and securely maintained at Zhongnan Hospital of Wuhan University under strict confidentiality and data security protocols.

To ensure data integrity and accessibility, the following measures will be implemented: (1) all investigators will receive standardized training on data management procedures prior to trial initiation; (2) responsible investigators will perform ongoing monitoring and periodic quality checks to assess data integrity throughout the study; (3) the principal investigator will oversee the data lifecycle and audit procedures.

### 2.9. Sample size and pilot trial rationale

This is a pilot study. The primary objectives are to assess the feasibility (recruitment, adherence) and safety of the oral yFMT, to evaluate the preliminary effciency, and to collect preliminary effect-size estimates for the planning of a subsequent pivotal trial.

As no prior data exist on achieving the composite glycemic target (TIR > 70% with TBR3.9 < 4%) following yFMT in adults with T1DM, a traditional sample size calculation based on an anticipated effect size was not feasible. The sample size for this trial was therefore determined in accordance with methodological best practices for pilot trial design. We referenced the guidance proposed by Wang et al., which indicates that a pilot study for a future definitive trial with 90% power and a two-sided alpha of 0.05 typically requires approximately 10–25 participants per group to provide meaningful parameter estimates for small-to-moderate effect sizes [23]. Based on this, and considering the common requirement for assessing primary feasibility objectives (e.g., recruitment rate, procedural acceptance), a sample size of 10 participants per group was set.

A pre-planned interim analysis will be conducted after the first 10 participants (50% of the total planned sample) have completed the 12-week follow-up. During this interim analysis, the DMC will review unblinded data, including safety outcomes and the primary composite endpoint, to evaluate safety and obtain preliminary treatment effect estimates for future sample size planning. No formal hypothesis testing will be performed, and no sample size re-estimation is planned for the current trial, consistent with its pilot nature. Based on the DMC’s review, the trial may continue as planned, be modified, or be terminated early if unacceptable safety concerns or clear futility are observed.

### 2.10. Statistics and analysis

Efficacy analyses will be performed in the intention-to-treat population. For the primary efficacy endpoint, participants with missing primary endpoint assessments will be considered non-responders using a non-responder imputation approach in the intention-to-treat analysis. Safety analyses will be performed in the safety analysis set. Normality of continuous variables will be assessed using the Shapiro-Wilk test at each time point. Normally distributed data will be presented as mean±standard deviation and analyzed using independent samples t-test (between-group) or paired t-test (within-group). Non-normally distributed data will be presented as median (Q1, Q3) and analyzed using Mann-Whitney U test (between-group) or Wilcoxon signed-rank test (within-group). Categorical data will be expressed as count (percentages) and analyzed using Fisher’s exact test.

For the primary efficacy endpoint assessed from baseline to Week 12 post-intervention, a generalized estimating equation (GEE) model with a binary distribution, logit link function, and an exchangeable correlation structure will be employed. The model includes group, time, and their interaction as fixed effects, with baseline composite achievement status as a covariates, as appropriate. Given the pilot nature of the study (n = 20), Fisher’s exact test will additionally be performed at each time point as a sensitivity analysis to ensure robustness. For continuous secondary outcomes, linear mixed-effects models will be applied with group, time, and their interaction as fixed effects, the baseline value of the respective outcome as a covariate, and age and T1DM duration as additional covariates, with a random intercept for each participant. Multicollinearity will be assessed using the variance inflation factor (VIF), with VIF > 10 indicating significant collinearity. Given the limited sample size, a parsimonious sensitivity model including only baseline value, group, and time will also be performed to assess robustness against overfitting. Feasibility outcomes will be assessed descriptively. All feasibility endpoints will be presented as frequencies and percentages, with 95% confidence intervals where appropriate. For secondary continuous outcomes and covariates, missing data will be addressed using multiple imputation. Twenty imputed datasets will be generated using baseline outcome values, age, T1DM duration, and treatment group as predictors, and results will be pooled using Rubin’s rules. Logistic regression analysis will be used to explore factors associated with response to yFMT treatment. CGM metrics, as recommended by international expert consensus, will be calculated using Glyculator 2.0 software (Medical University of Lodz, Poland). All statistical analyses will be performed using R software (version 4.3.2) and GraphPad Prism 9.0. Statistical significance is defined as two-sided *P* < 0.05. Bonferroni correction will be applied for multiple comparisons in post hoc analyses.

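### Section 2.10 gives continuous secondary outcomes two between-group analyses, a pre-tested t/Mann-Whitney test and a baseline-adjusted mixed model, without saying which decides

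*Protocol article*

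**What the plan says.** All the relevant text is in section 2.10 of the protocol article.

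- **Route A, simple tests.** "Normality of continuous variables will be assessed using the Shapiro-Wilk test at each time point". Data judged normal are "analyzed using independent samples t-test (between-group) or paired t-test (within-group"); other data are "analyzed using Mann-Whitney U test (between-group) or Wilcoxon signed-rank test (within-group").
- **Route B, mixed model.** "For continuous secondary outcomes, linear mixed-effects models will be applied with group, time, and their interaction as fixed effects". The model also has the outcome's baseline value, age and T1DM duration as covariates, and a random intercept.
- **Labels.** For continuous outcomes, only the reduced mixed model is called a sensitivity analysis: "a parsimonious sensitivity model including only baseline value, group, and time will also be performed to assess robustness against overfitting". For the binary primary endpoint the order is explicit, with the GEE model first and then "Fisher’s exact test will additionally be performed at each time point as a sensitivity analysis to ensure robustness". Route A has no label.
- **Threshold.** "Statistical significance is defined as two-sided *P* < 0.05". The only multiplicity rule is "Bonferroni correction will be applied for multiple comparisons in post hoc analyses".

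Section 2.9 sets 10 participants per group. Table 3 in section 2.5 lists most secondary outcomes at both Week 4 and Week 12, and its note defines them as changes relative to baseline.

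**The concern.** Each continuous secondary outcome at each visit can receive two between-arm P values that answer slightly different questions, and either could later be cited as prespecified. This is separate from multiplicity across the many outcomes: it arises within one outcome at one visit.

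Route A also lets the data choose the test. With 10 per arm, the same outcome may be compared on means at Week 4 and on ranks at Week 12. That suits section 2.9 poorly, because one aim there is to collect effect-size estimates for a later trial, and a mean difference at one visit and a rank comparison at the other do not form one planning estimate. Route A also fits awkwardly with the multiple imputation planned for these outcomes. Rubin's rules pool estimates with standard errors, which a Mann-Whitney test does not directly supply, and the normality result could differ across the 20 imputed datasets.

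**Working it through.** **Inputs from the protocol article:** 10 per arm; baseline, Week 4 and Week 12; two-sided 0.05; the two routes as described in section 2.10.

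**Assumptions not in the documents:** complete data; equal correlation ρ between the three measurements (0.5, 0.7, 0.8; some null runs also used 0.3); normal data, or log-normal data as exp(0.7z); a true effect, where there is one, of 1 SD at both post-baseline visits; age and duration unrelated to outcome.

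**Simulated analyses.** Route A: Shapiro-Wilk in each arm, then a t-test if both pass and Mann-Whitney otherwise, on raw Week 12 values or on change from baseline. Route B: the Week 12 group contrast of the random-intercept model with the three covariates and Satterthwaite degrees of freedom.

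**1. Nominal level.** Under no effect, each route alone is significant in about 4–6% of trials, in line with the stated 0.05. The pre-test does not by itself inflate the error.

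**2. Either route significant, no effect.** Two independent tests would give 1 − 0.95² = 0.0975. The two routes share data, so the figure is lower: about 7–9% at Week 12, for normal and log-normal data and for raw values and change scores alike. With one deciding analysis it returns to about 5% (simulated mixed model 4.2–5.3%).

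**3. Switching of test between visits.** With normal data both arms pass with probability 0.95² = 0.9025 (simulated 0.90). If the visits were independent, the choice would differ with probability 2 × 0.9025 × 0.0975 = 0.176; the simulated figure is about 15–19%. With log-normal data both arms pass in only about 36% of trials on raw values and about 60% on change scores. Independence would give 2 × 0.36 × 0.64 = 0.46 and 2 × 0.60 × 0.40 = 0.48; with correlated visits the simulated figure is about 34–43%.

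**4. Power with a 1 SD effect, normal data.** For a t-test the noncentrality is (effect/SD) × √(10/2), on 18 degrees of freedom.

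- Raw values: SD = 1, noncentrality 2.236, power 56% at every ρ.
- Change scores: SD = √(2(1 − ρ)) = 1.000, 0.775, 0.632 at ρ = 0.5, 0.7, 0.8; noncentrality 2.236, 2.887, 3.536; power 56%, 78%, 92%.

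The simulation of the full Route A and Route B agrees:

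| | ρ = 0.5 | ρ = 0.7 | ρ = 0.8 |
|---|---|---|---|
| Mixed model, power | 64% | 80% | 92% |
| Route A on change, power | 55% | 77% | 92% |
| Route A on raw values, power | 57% | 56% | 56% |
| Disagreement, Route A on change | 21% | 14% | 6% |
| Disagreement, Route A on raw values | 22% | 31% | 39% |

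On change scores, Route A loses 64 − 55 = 9 points at ρ = 0.5, 80 − 77 = 3 points at ρ = 0.7, and nothing visible at ρ = 0.8.

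**The case against.** The strongest reply is that the section already implies an order. The Shapiro-Wilk text is a general account of how continuous variables are summarised and compared, while the mixed-model sentence is specific to continuous secondary outcomes. The only sensitivity analysis for those outcomes is a reduced mixed model, and the planned imputation with pooling suits model estimates. This stands as the more natural reading. It does not remove the point: the general text prescribes named between-group tests, does not confine them to description, and is left unlabelled in a section that labels its other secondary checks.

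A reader might infer that the simple tests ignore baseline, lose much power, and disagree with the model in up to 39% of trials. The documents do not support that. The Table 3 note defines these endpoints as changes from baseline, so Route A would most naturally be run on change scores. Baseline is then subtracted, though not adjusted for, and the power loss and disagreement are much smaller. The large figures hold only for raw visit values.

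A reader might also infer that the plan will report whichever result is significant. Nothing says so. The 7–9% applies only if either result may be cited; if both are reported side by side, readers can see any discrepancy.

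Finally, the choice of transformation for individual analytes is ordinary analysis-plan detail, and its absence is not a finding. The finding is that two between-group analyses are both stated, with no rule between them.

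**Conclusion.** The point holds as an unresolved overlap in the stated text, with modest consequences. If either route may be cited, the Week 12 error per outcome is about 7–9% instead of 5%. The data-driven choice changes the test between visits in about 15–19% of trials with normal data and 34–43% with log-normal data. With a true 1 SD effect the routes disagree in about 21% of trials at a correlation of 0.5, falling to 6% at 0.8, if Route A uses change from baseline; on raw values the range is about 21–39%.

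All these figures rest on the assumed correlations, distributions and effect size. The null excess appeared in every scenario run. Severity is low to moderate: the outcomes are secondary, the trial is a 20-person pilot, and no stated decision depends on a secondary P value.

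**What to change.** In section 2.10:

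- Name the baseline-adjusted mixed model's Week 12 between-arm contrast as the single deciding between-group analysis for each continuous secondary outcome, with the Week 4 contrast secondary.
- Remove the choice of test by Shapiro-Wilk.
- Keep the t-test and Mann-Whitney test only as a labelled supportive check, stating that they are applied to change from baseline, or drop them.
- Handle markedly skewed outcomes by a log transformation fixed before unblinding.

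The cost is a wording change, with no effect on data collection or conduct. The one real burden is that the transformations must be chosen in advance. Section 2.2 reports recruitment as ongoing and section 2.1 keeps the study blinded until database lock, so the change can still be made before the investigators know any results by arm.

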## 1. Introduction

Type 1 diabetes mellitus (T1DM) is a chronic autoimmune disease characterized by the destruction of pancreatic β cells and lifelong insulin dependence [1]. Although advances in insulin analogs, delivery modalities, and continuous glucose monitoring (CGM) systems have improved diabetes management, people with T1DM still face challenges such as suboptimal glycemic outcomes, frequent episodes of hypoglycemia, and a high burden of self-management [2–7].

The core pathological mechanism of T1DM involves autoimmune-mediated destruction of pancreatic β cells. Conventional insulin therapy fails to halt the autoimmune process or restore β-cell function. In recent years, the gut microbiota, termed the “second genome,” has been recognized as an important contributor to T1DM pathogenesis [8]. Numerous studies have characterized gut microbiota alterations in individuals with T1DM, marked by a reduction in butyrate-producing bacteria and secondary bile acids, along with an increase in pathobionts [9–11]. Impaired intestinal barrier function represents another hallmark of this dysbiotic state, and together these features contribute to disruption of the “gut microbiota-intestinal-islet axis” [11].

Fecal microbiota transplantation (FMT) is a promising technique that transfers healthy donor microbiota to a recipient, aiming to restore microbial homeostasis. Evidence from animal studies has demonstrated that modulation of the gut microbiota can improve glycemic control through multiple mechanisms, including enhancement of intestinal barrier integrity, increased production of short-chain fatty acids, regulation of immune responses, and preservation of residual β-cell function [12,13].

Clinical evidence supports the potential of FMT in enhancing glycemic control among patients with T1DM. In a randomized controlled trial (RCT), both autologous and allogeneic FMT groups exhibited a reduction in glycated hemoglobin (HbA1c) at 12 months, without significant changes in insulin dosages [14]. Additionally, clinical studies demonstrate that washed microbiota transplantation significantly increases the time in range (TIR) and reduces glycemic variability among adults with T1DM [15,16]. Together with two capsule-based RCTs [17,18], these studies showed that FMT was generally safe, with mild and transient gastrointestinal symptoms being the most frequent adverse events [14–18].

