(2) Bowel Preparation: from Day −3, participants receive oral rifaximin (0.2 g per dose, four times daily), with bowel preparation using a polyethylene glycol solution performed on Day 0.

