#### 2.4.4. Study intervention.

(1) Regimen: The yFMT capsules are manufactured by Meiyitian Biomedical Co., Ltd. (Wuhan, Hubei, China) and prepared from rigorously screened healthy young donors (aged 4–17 years), selected for the relatively high temporal stability of the gut microbiota during this developmental window [19,20]. Donor-recipient matching follows a three-dimensional framework based on disease state, sex, and age (Fig 3). All donor screening, infectious disease testing, and microbiological safety procedures comply with the Chinese expert consensus on FMT donor management [21], with dual informed consent obtained from both donors (when age-appropriate) and their legal guardians. Eligible participants will be randomized to receive either yFMT capsules or identical capsules (skimmed milk and starch). The administration protocol is as follows: 6 capsules are to be taken orally twice daily (a total of 12 capsules/day) under fasting conditions (at least 2 hours before or after meals) for six consecutive days, delivering a total cumulative dose of approximately 2.0 × 10^^^ [13] viable bacteria per course [22]. All capsules must be swallowed whole without chewing to maintain bacterial viability and blinding. All participants maintain their usual insulin therapy throughout the study period and are allowed to adjust their insulin dose based on CGM data.(2) Storage and Handling: Capsules are stored at −80°C and must be administered within 20 minutes of thawing.(3) Safety Monitoring: During the 6-day intervention period, participants will be monitored daily for:a. Gastrointestinal tolerance: specifically assessing bloating, abdominal pain, changes in bowel habits (constipation or diarrhea), nausea, or vomiting.b. Systemic symptoms: fever, rash, or any new allergic-like reactions.c. Glucose metabolism: close review of CGM data for significant or unexplained glycemic fluctuations, particularly hypoglycemia.

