	Intervention adherence
	Acceptability
**Safety endpoints**	Number of adverse events and serious adverse events

**Note:** All changes in the above-mentioned indicators are relative to baseline values. Glycemic parameters: including HbA1c, FBG, MMT 2h PG and other CGM metrics [TIR, TBR3.9, TAR, GMI, GRI, CV]; Pancreatic β-cell function: Including FCP, MMT 2h CP, and the AUC of MMT 2h CP; Insulin sensitivity indicators: Including eGDR; Infection and inflammatory markers: Including WBC, PCT, ESR, hs-CRP, and inflammatory cytokines; Intestinal Barrier-Related Antibodies: Including Anti-LPS, Anti-Occludin Antibodies; Cellular immune indicators: Including peripheral blood Treg/Th17 ratio and islet-related autoantibodies [GADA, IA-2A, ICA]; Lipid profile: Including TC, TG, LDL-c, and HDL-c; Serum metabolomic profiles: Including bile acids [e.g., UDCA, TUDCA] and SCFAs; PROs: Including EQ-5D-5L, CHFSII-WS, and DDS; Recruitment rate: Proportion of screened participants enrolled; Retention rate: Proportion of participants completing the 12-week follow-up; Intervention adherence: Percentage of prescribed capsules consumed; Acceptability; Participant-reported tolerability and willingness to undergo treatment. Serious adverse events: Including severe hypoglycemia, diabetic ketoacidosis and severe allergic reactions;

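### Within-arm paired tests on continuous secondary outcomes share the two-sided 0.05 threshold and are not labeled descriptive, although both arms can change after baseline with no yFMT effect

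*Protocol article*

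**What the plan says.** Section 2.10 chooses tests for continuous variables by distribution. Normally distributed data are "analyzed using independent samples t-test (between-group) or paired t-test (within-group"; other data are "analyzed using Mann-Whitney U test (between-group) or Wilcoxon signed-rank test (within-group". The same section sets one criterion, "Statistical significance is defined as two-sided *P* < 0.05", and its only multiplicity rule is that "Bonferroni correction will be applied for multiple comparisons in post hoc analyses". Feasibility outcomes are explicitly to be handled descriptively. The within-arm tests carry no such label.

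Section 2.10 also plans between-group models: a GEE with group, time and their interaction for the primary endpoint, and linear mixed models with the same terms plus the baseline value for continuous secondary outcomes.

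The note to Table 3 (Section 2.5) defines every endpoint as a change: "All changes in the above-mentioned indicators are relative to baseline values". Section 2.4.2 has the non-CGM baseline assessments, including microbiome, metabolomics, barrier and immune markers, finished by Day −3. After that, "participants receive oral rifaximin" from Day −3, with polyethylene glycol cleansing on Day 0. Randomization follows the run-in (Section 2.4.3), so both arms go through these steps. Under Section 2.4.4, participants in both arms "are allowed to adjust their insulin dose based on CGM data".

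**The concern.** The trial asks whether yFMT does more than placebo. A paired t-test or signed-rank test inside the yFMT arm has a different null, that the arm has not changed since baseline. In this design the null can fail in both arms for reasons that have nothing to do with yFMT:

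- An antibiotic course and bowel cleansing lie between the baseline stool and blood samples and every follow-up sample.
- Insulin is being optimized during the CGM baseline window (Day −17 to −3), and doses may change afterwards.
- Entry requires HbA1c of 7.0–14.0% or TIR below 70%. The note to Fig 1 applies this to the run-in CGM and the Day −3 HbA1c, which are themselves the baseline, so some regression to the mean can be expected in both arms.

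Every endpoint is a change from baseline, so a within-arm P value looks like an endpoint result. At stake is how the microbiota, metabolomic, immune and glycemic secondary results are read. A significant change with yFMT, or significance with yFMT but not with placebo, could pass for a yFMT effect when the two arms changed equally.

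**Working it through.** **Inputs from the protocol article.** 10 participants per arm (Section 2.9), 1:1 allocation (Section 2.4.3), two-sided 0.05 (Section 2.10). The article derives no power figure that could be reproduced; the sample size comes from pilot-trial guidance.

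**Assumptions.** The yFMT effect is zero. Individual changes are normal. Both arms have the same mean change, equal to δ times the SD of the individual changes. The documents give no value for δ, so a range from 0 to 1.0 is shown.

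**Step 1: the paired test in one arm.** With n = 10 the statistic follows a noncentral t distribution with 9 degrees of freedom and noncentrality δ√10. The rejection probability is p = P(|T| > t₀.₉₇₅,₉). For δ = 0.5 the noncentrality is 0.5 × 3.162 = 1.58, which gives p = 0.293.

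**Step 2: split verdicts.** The arms are independent with the same p. The chance of yFMT significant and placebo not is therefore p(1 − p). The chance that exactly one arm is significant is 2p(1 − p).

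| δ (assumed) | p | p(1 − p) | 2p(1 − p) |
|---|---|---|---|
| 0 | 0.050 | 0.050 × 0.950 = 0.048 | 0.095 |
| 0.25 | 0.109 | 0.109 × 0.891 = 0.097 | 0.194 |
| 0.5 | 0.293 | 0.293 × 0.707 = 0.207 | 0.414 |
| 0.75 | 0.562 | 0.562 × 0.438 = 0.246 | 0.492 |
| 1.0 | 0.803 | 0.803 × 0.197 = 0.158 | 0.316 |

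The yFMT-only pattern peaks in the middle of the range, because with a large common shift both arms tend to be significant.

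**Step 3: the between-group test on the same changes.** In 100,000 simulated trials per setting, a two-sample t-test on change rejected in 4.9%, 5.0% and 5.0% of trials at δ = 0, 0.5 and 0.8. The common shift cancels, so the rejection rate stays near 5%.

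**The case against.** The strongest reply is that Section 2.10 already contains the right analysis. The list of tests by data type is generic. The endpoint analyses are the GEE and the mixed models with group-by-time terms and baseline adjustment. A paired test is a valid test of change and misleads only if misread. This stands, and it limits the point to wording and reporting. It does not remove it, because the within-arm tests are planned under the same threshold as the rest and add nothing that the models need.

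A reader might infer more than the documents support:

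- *That the plan will judge yFMT on within-arm P values.* No passage ties a conclusion about yFMT to a paired test.
- *That the primary endpoint is compromised.* It is binary, and the paired t and signed-rank tests are listed only for continuous data.
- *That the type I error rises to 80%.* If an arm truly changed, rejecting no change is power. The error would lie in attributing that change to yFMT.
- *That the standardized diet is another post-baseline cause.* It is stated only for Day −17 to −3, the CGM baseline window itself.
- *That the Introduction already makes this mistake.* It reports that "both autologous and allogeneic FMT groups exhibited a reduction in glycated hemoglobin (HbA1c) at 12 months", but both arms of that trial received FMT, and background text is not an analysis rule.

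The percentages also depend on assumed shifts. At 0.25 SD they are modest, and nothing in the documents shows that every marker moves by 0.5 SD or more by Week 12.

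Finally, an unseen analysis plan might label these tests descriptive. That is possible, but the article states the tests and the threshold, so the point concerns what is written and not only what is absent.

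**Conclusion.** The point holds in a limited form. For continuous secondary outcomes, Section 2.10 plans within-arm significance tests that can reject when yFMT does nothing, and it does not set them apart from the tests that compare the arms. That both arms are exposed to causes of change follows from the protocol's own timing of baseline, rifaximin, cleansing, insulin adjustment and entry criteria. How large the change will be is unknown. Across assumed common shifts of 0.25 to 1.0 SD, the yFMT paired test is significant in 11% to 80% of trials, and the yFMT-only pattern appears in 10% to 25%. With no shift both figures are about 5%. These results assume normal changes, equal shifts and 10 evaluable participants per arm. They illustrate the risk and do not predict this trial's results. The correction is worth making because it is specific, nearly free and removes a source of misleading evidence.

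**What to change.** In Section 2.10, replace the within-group paired t-test and Wilcoxon signed-rank test with a statement that within-arm changes are descriptive: an estimate with its 95% CI for each arm, and no P value. Add that any claim about a yFMT effect, including on microbiota, metabolomic and immune outcomes, rests on the between-group, baseline-adjusted contrast from the models already planned.

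The cost is one or two sentences, with no new data and no new model. The downside is fewer P values to report. Section 2.1 keeps the study blinded until database lock, so the edit should be made before then.

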### 2.3. Participants

Participant recruitment will be conducted from November 2025 to July 2026. Eligible participants aged 18–60 years must have a T1DM duration of more than one year and suboptimal glycemic outcomes, defined as HbA1c of 7.0–14.0% within the past three months or 14-day CGM-derived TIR < 70% within the past month. Participants will be excluded if they had recent episodes of diabetic ketoacidosis, concurrent severe gastrointestinal diseases, significant gastrointestinal surgery, pregnancy, or lactation. The diagnosis of T1DM adheres to the criteria established by the World Health Organization and the American Diabetes Association. Full criteria are listed in Table 1.

**Table 1 pone.0343078.t001:** Inclusion and exclusion criteria for enrollment.

Inclusion Criteria	
1	T1DM was diagnosed by an endocrinologist for at least 1 year
2	Aged 18–60 years (inclusive)
3	HbA1c between 7.0 to 14.0% (within past 3 months) or TIR < 70% (14-day CGM within the past month)
4	On MDI or insulin pump therapy for ≥3 months
5	TDD before admission ≥0.3 IU/kg/day, with a basal rate ≥0.05 IU/hour
6	Women of childbearing age are willing to use appropriate contraceptive measures
7	Signed informed consent form

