#### 2.4.3. Randomization and blinding.

Following the completion of the run-in period, eligible participants will be randomized in a 1:1 ratio to either the intervention or the control group. Randomized allocation sequences will be generated using a permuted block design in R software. Sequentially numbered, opaque, sealed envelopes will be prepared and stored by a non-investigational team member. To minimize selection bias, the randomization codes are assigned by an independent researcher. Once an eligible participant is enrolled, the principal investigator notifies the independent researcher to open sequentially the sealed envelope for allocation. yFMT and placebo capsules are identical in appearance, shape, odor, and specifications.

The investigational capsules will be assigned predefined random codes that were dispensed without selection. Randomization number is not allowed to be reassigned following participant discontinuation. The randomization code will be securely maintained by an independent statistician throughout the study. The code will remain inaccessible to investigators, participants, and endpoint assessors, except for authorized access by the independent Data Monitoring Committee (DMC) during the pre-specified interim analysis. Full unblinding will occur only after database lock and completion of the final analysis.

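### With 10 participants per arm, the primary logit GEE has no finite Week 12 odds ratio if either arm has 0/10 or 10/10 achievers, and the plan names no result to govern in its place

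*Protocol article*

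**What the plan says.** Section 2.10 of the protocol article fixes the primary model: "a generalized estimating equation (GEE) model with a binary distribution, logit link function, and an exchangeable correlation structure will be employed". Its fixed effects are group, time and group-by-time, with baseline achievement status as a covariate where appropriate. The outcome is yes or no: TIR above 70% together with TBR3.9 below 4%. Missing outcomes count as non-response. Section 2.10 adds that Fisher's exact test "will additionally be performed at each time point as a sensitivity analysis to ensure robustness". It also says "Statistical significance is defined as two-sided" P < 0.05.

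On size, section 2.9 says that "a sample size of 10 participants per group was set". It gives no rate or effect for the composite: "As no prior data exist on achieving the composite glycemic target" after this treatment, so "a traditional sample size calculation based on an anticipated effect size was not feasible". Entry (Table 1, inclusion 3) requires "HbA1c between 7.0 to 14.0% (within past 3 months) or TIR < 70% (14-day CGM within the past month").

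**The concern.** Group-by-time gives each arm at each visit its own log-odds. With 10 people behind each one, a cell of 0/10 or 10/10 is a realistic result, and its log-odds is minus or plus infinity. Software rarely says so plainly. It may stop at some large coefficient and print a standard error and a P value, or it may print none.

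Several features of the trial push counts towards zero. The endpoint needs two conditions at once. Missing outcomes count as failures. Under the Fig 1 note, anyone who enters on run-in TIR below 70% is a baseline non-achiever by definition.

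Two things are at stake. One is the effect estimate that section 2.9 wants for planning the next trial. The other is the significance statement that section 2.10 attaches to the primary model. If a tiny GEE P stood next to a Fisher P near 1, the stated hierarchy would favour the wrong one.

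**Working it through.** **Inputs.** 10 per arm, allocated 1:1 (sections 2.9 and 2.4.3); logit GEE with group-by-time and two-sided 0.05 (section 2.10). The achievement rate is not given, so 5% to 40% is assumed. There is no power calculation to reproduce. The plan's own total checks: 2 × 10 = 20.

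**Step 1: why no solution exists.** With complete data and no extra covariate, the fitted proportion in each arm-by-visit cell equals the observed one. The Week 12 log OR is therefore ln[x1/(10 − x1)] − ln[x0/(10 − x0)].

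- For 2/10 v 5/10: ln(5/5) − ln(2/8) = 1.39, OR 4, robust SE 1.01, P = 0.17. The fit is ordinary.
- For 0/10 v 1/10 the second term is ln(0). Fitting the Week 12 table by the usual iterations gives:

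| Iterations | log OR | OR | Robust SE | Robust Wald P |
|---|---|---|---|---|
| 5 | 4.00 | 55 | 1.10 | 0.0003 |
| 10 | 9.01 | 8,150 | 1.10 | 3 × 10⁻¹⁶ |
| 25 | 24.01 | 2.7 × 10¹⁰ | 1.05 | 8 × 10⁻¹¹⁵ |

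Fisher's P for this table is 1.00. A model-based SE goes the other way, from 7.1 (P = 0.57) at 5 iterations to 85.6 (P = 0.92) at 10. Full exchangeable GEE fits with an empty Week 12 cell stopped at a log OR of 28 to 31 with an undefined SE. Adding baseline status as a covariate did not help; that fit diverged.

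**Step 2: how often at Week 12.** For one arm, q = (1 − p)¹⁰ + p¹⁰. For at least one of two arms, 1 − (1 − q)².

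| Rate in both arms | q | At least one arm 0/10 or 10/10 |
|---|---|---|
| 5% | 0.5987 | 83.9% |
| 10% | 0.3487 | 57.6% |
| 15% | 0.1969 | 35.5% |
| 20% | 0.1074 | 20.3% |
| 30% | 0.0283 | 5.6% |
| 40% | 0.0062 | 1.2% |

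At 10% v 30%: 1 − (1 − 0.3487)(1 − 0.0283) = 36.7%.

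**Step 3: what the P value does when there is no effect.** Simulated null trials used Weeks 4 and 12 as outcomes, baseline status as covariate, latent correlation 0.5 and Python statsmodels, with a few hundred trials per setting.

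| Rate | P < 0.05 | No P value |
|---|---|---|
| 10% | about 25–28% | about 20–24% |
| 20% | about 10–11% | about 13–18% |
| 30% | about 4% | about 7% |

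Fisher's test gave P < 0.05 in 0–1%. A separately coded GEE gave 40–44% at 10% and 17–24% at 20%. This dependence on software is expected where no solution exists. The plan's software is R, so these figures show the order of size and are not a forecast.

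**Step 4: which cell is empty.** A cell empty only at Week 4 or only at baseline left the Week 12 between-arm log OR finite (1.79 and 1.39 in worked examples), though the interaction and standard errors could break down. If baseline is itself an outcome row, the effect is the interaction from baseline, and an empty baseline cell makes that infinite too. Section 2.10 allows either reading: it describes the endpoint as running from baseline, yet also makes baseline status a covariate.

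**Step 5: finite alternatives on the same data.** For 0/10 v 1/10, the Wilson limits are 0 to 0.2775 and 0.0179 to 0.4042. The Newcombe interval for the difference of 0.10 is then:

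- lower: 0.10 − √[(0.10 − 0.0179)² + 0.2775²] = −0.19
- upper: 0.10 + (0.4042 − 0.10) = 0.40

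The Firth-type OR is 3.3 (95% CI 0.12 to 92), P = 0.48. Both can be interpreted.

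**The case against.** The strongest objection is about frequency. The documents give no achievement rate, and the range above runs from 84% to 1%. Insulin is optimised and diet standardised before randomisation (section 2.4.2), and insulin may be adjusted on CGM data throughout (section 2.4.4). Rates of 20–30% are therefore as defensible as 5–10%. This stands: a reader might infer that failure is likely at n = 20, but the documents do not support that.

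A reader might also infer that empty baseline cells are the rule. They do not show that either. Entry is by HbA1c or TIR, so someone admitted on HbA1c can already meet the target, and baseline may be only a covariate. Nor does an empty cell at any visit ruin the primary result, as Step 4 shows.

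The harm is also softened. Counts, percentages and Fisher's test at each time point are planned, so Week 12 proportions will be available whatever the GEE does, and a false GEE P would be visible beside them. Section 2.9 names feasibility and safety as objectives alongside preliminary efficacy, so the trial does not stand or fall on this estimate.

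Finally, a rule for non-convergence is often left to a SAP, which is not shown. That answers only part of the point. The article itself fixes the model as primary and Fisher's test as sensitivity. Fisher's test is unadjusted, yields no finite OR with an empty arm, and is not said to take over.

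**Conclusion.** The point holds in conditional form. If either arm has 0/10 or 10/10 achievers at Week 12, the stated primary model has no finite Week 12 odds ratio, and its P value can be falsely small. That much is certain. How often it happens depends on an achievement rate that the documents do not give. It is more likely than not at about 10% or below in both arms, about one in five at 20%, and uncommon at 30% or above. The calculations assume 10 analysed per arm and, except for the 10% v 30% case, equal rates; the simulations also assume a latent correlation of 0.5 and one software package. Because a valid exact test and the raw proportions are already planned, this is a should-fix matter and does not threaten the trial as a whole.

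**What to change.** In section 2.10:

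- Make the primary Week 12 result the difference in achievement proportions with a small-sample 95% CI, such as Newcombe or Miettinen-Nurminen.
- Take the P value from Fisher's exact test. If an adjusted estimate is wanted, use a Firth-penalised logistic model with baseline status.
- Keep the GEE as supportive, reported only when every arm-by-visit cell has at least one achiever and one non-achiever.
- State that baseline status is a covariate and not an outcome row.

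The choice among these methods is partly preference. The least that would close the gap is one sentence saying that the Week 12 proportions and Fisher's test govern when an arm is empty or full.

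The cost is wording only, and recruitment is still open, so it can be settled before unblinding. There are downsides. The simple difference is unadjusted. Exact and penalised tests are conservative at low rates (simulated size of the Firth test about 1.5% at a 12% rate). The interval and the exact test can also disagree. For 0/10 v 4/10, the Newcombe lower limit is 0.40 − √[(0.40 − 0.1682)² + 0.2775²] = 0.04, above zero, while Fisher's P is 0.087. The text should say which of the two carries the conclusion.
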